### Statistical analysis plan

Baseline data will be summarized using descriptive statistics and percentages. No hypothesis testing will be performed on baseline data. However comparability of the LGAs will be evaluated from the perspective of clinically meaningful differences. The primary outcome SBA will be analyzed. The outcome data will be aggregated to the cluster level and analyzed with regression model to examine the determinants of skilled pregnancy care using PHCs. The Statistical Package for Social Science (SPSS) version 22.0 (SPSS Inc., Chicago, IL, USA) will be used to enter and analyse the data.

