**Methods:**

An open-labelled, randomized controlled trial will is carried out in two local government areas selected based on three criteria (i) maternal mortality rates (ii) PHC utilization rates and (iii) and geographic localization. The study will be conducted over 54-months in six communities, with PHCs in six communities of similar status serving as control sites. Surveys about quality of care and maternal health services utilization will be carried out at baseline, at midterm and at end of the project to test the effectiveness of the intervention, alongside conventional epidemiological measures of maternal and perinatal mortality. Ethical approval for the study has been granted (reference no. NHREC/01/01/2007). The findings will be published in compliance with reporting guidelines for randomized controlled trials.

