Despite the provision of free maternal care services, the experience in many states has been that health care utilization initially increased in some states, but this has not been sustained over time. Many health providers and women voiced concern that despite the free services, many health facilities lacked basic facilities, the health care personnel were poorly motivated, while many of the pre-existing challenges that led to poor utilization remained [19, 20]. The exception was Ondo State, which witnessed sustained and unparalleled transformation of maternal care, with the State achieving MDG-5 status, the only state to do so in the country. This was due to the institutionalisation of the *Abiye* program [21, 22]*,* which addressed both the demand and supply factors contributing to access barriers in a composite and multi-faceted manner. Under Abiye, the government provided free antenatal and delivery care, linked pregnant women to health providers through mobile phones and improved clinical service delivery at secondary health facilities. However, the fact that this intervention focussed on secondary care facilities (first referral level) only and was mainly located in urban areas without a research strategy to compare results with control sites diminished the policy relevance of this approach.

Evidence abounds to show that unskilled delivery dramatically increases the risk of maternal and perinatal death, as women who die during pregnancy, or who experience perinatal deaths, are often those not receiving antenatal, intrapartum and postnatal care, and those whose deliveries are attended by an unskilled birth attendant or who deliver at home [20–22]. National data from the Demographic and Health Survey [23] indicate that less than 65% of Nigerian women receive antenatal care during pregnancy, less than 33% are attended to by skilled birth attendants (SBA) at the time of delivery, and under 40% receive follow-up postnatal care.

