### Data source and sampling

A combination of secondary and primary data is required for the study. The sample size formula below is applied for the formative research survey as follows:

n_1_ = {[p_1_q_1_ + p_o_q_o_]) (Z_α/2_ + Z_β_)^2^}/ (p_1_-po)^2^.

p_0_ = utilization of PHC for maternal and perinatal in the control arm (assumed to be − 5 reduction in the prevalence in the experiment site).

p_1_ = utilization of PHC for maternal and perinatal care in the experimental arm.

*z*_*α*_ = Two-sided standard normal variate at 95% level of significance = 1.96.

*z*_*β*_ = Statistical power at 80% = 0.84;

n_1_ = n_2_.

n_1_ = no of study participants in the experimental group.

n^2^ = no of study participants in the control group.

We assume 50% since there is no literature from the geographical location of the study which reported the prevalence of utilization of PHCs for maternal and perinatal health care. Thus;

n^1^ = (0.50 × 1–0.50 + 0.45 × 1–0.45) (1.96/2 + 0.84)^2^/(0.50–0.45) 2.

(0.25 + 0.2475) (3.3124)/0.0025.

n^1^ = 659.

n^2^ = 659.

Total sample size = 1318.

10% adjustment for non-response = 132.

Total = 1450.

There will be 725 respondents in the experiment LGA and 725 in the control LGA.

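### The only sample size is built on PHC use at 50% against 45%, but the declared primary outcome is skilled birth attendance, which has no planning rate, target difference or power

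*Protocol article*

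**What the plan says.** Three places in the protocol article bear on this.

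- **Data source and sampling.** The two planning proportions are "utilization of PHC for maternal and perinatal in the control arm" and "utilization of PHC for maternal and perinatal care in the experimental arm". The experimental value is set by default: "We assume 50% since there is no literature from the geographical location of the study which reported the prevalence of utilization of PHCs". The control value is 5 points lower, at 45%. The section uses two-sided 5% significance and 80% power, and arrives at 659 per arm, 1,318 in total, and 1,450 after an allowance for non-response. That is 725 in an experimental LGA and 725 in a control LGA. The section opens, however, with: "The sample size formula below is applied for the formative research survey as follows".
- **Statistical analysis plan.** "The primary outcome SBA will be analyzed". The next sentence describes a cluster-level regression whose stated aim is to find what determines skilled care in pregnancy delivered through PHCs.
- **Background.** SBA is expanded as skilled birth attendance. The only rate given for it is national: "less than 33% are attended to by skilled birth attendants (SBA) at the time of delivery".

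The article gives no SBA control rate, SBA target difference or SBA power, and nowhere says that PHC use stands in for SBA.

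**The concern.** The quantity that was sized and the quantity declared primary are different measurements, and in this trial they can move apart.

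- SBA is about who attends the birth. PHC use is about the type of facility, and as worded in the sample size it covers care beyond the birth.
- The Background describes three tiers of care, with complex cases passed up to hospitals. A hospital birth is attended by skilled staff but is not a PHC birth.
- Under Intervention design, the package promotes family planning, antenatal, delivery and postnatal services, and trains providers and traditional birth attendants to refer. It could raise antenatal use of PHCs with little change in SBA, or raise SBA in hospitals with little change in PHC use.

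What is at stake is the meaning of the stated power. A reader who takes 80% power and 725 per LGA as the trial's planning claim will attach them to SBA, the declared primary outcome, when no SBA figure entered the calculation. A null SBA result could not be interpreted against any planned detectable difference.

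**Working it through.** **Inputs.** From Data source and sampling: p1 = 0.50, p0 = 0.45, z for significance 1.96, z for power 0.84. From Background: SBA below 33% nationally. Assumption: the 5-point difference is carried over to SBA, because the article gives none.

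**Step 1: reproduce the plan's figure.** The printed formula is n = (p1q1 + p0q0)(z_α/2 + z_β)² / (p1 − p0)².

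- p1q1 + p0q0 = 0.25 + 0.2475 = 0.4975
- z term as printed: (1.96/2 + 0.84)² = 1.82² = 3.3124
- n = 0.4975 × 3.3124 / 0.0025 = 659.2

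This matches the stated 659. Then 2 × 659 = 1,318, and 1,318 + 132 = 1,450. Only PHC-use proportions enter. The value 1.96 is already the two-sided 5% value, so halving it is an error in its own right. With (1.96 + 0.84)² = 7.84, the same proportions give 0.4975 × 7.84 / 0.0025 = 1,560.2, so 1,561 per arm.

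**Step 2: isolate the effect of the endpoint.** The z term must be held fixed while the proportions change. Power at 659 per arm is approximately Φ(0.05 / √[(p1q1 + p0q0)/659] − 1.96). None of these figures allows for clustering. The z-term columns are rounded up, which is why the first row shows 660 where the plan prints 659.

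| Scenario | p1q1 + p0q0 | n per arm, z term 7.84 | n per arm, z term 3.3124 | Power at 659 per arm |
|---|---|---|---|---|
| PHC use, 50% v 45% (plan) | 0.4975 | 1,561 | 660 | Φ(1.820 − 1.96) ≈ 44% |
| SBA, 38% v 33% (assumed) | 0.2356 + 0.2211 = 0.4567 | 1,433 | 606 | Φ(1.899 − 1.96) ≈ 48% |
| SBA, 33% v 28% (assumed) | 0.2211 + 0.2016 = 0.4227 | 1,326 | 561 | Φ(1.974 − 1.96) ≈ 51% |
| SBA, 25% v 20% (assumed) | 0.1875 + 0.1600 = 0.3475 | 1,090 | 461 | Φ(2.177 − 1.96) ≈ 59% |

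**Step 3: read across.** In either n column, moving from the PHC-use row to an SBA row lowers the requirement. With the correct z term the fall is 1 − 1,433/1,561 = 8% for 38% v 33%, and 1 − 1,326/1,561 = 15% for 33% v 28%. The large gap lies between the two n columns, and that gap is the halved 1.96.

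**The case against.** **The calculation may not be meant for the trial.** The section labels it as for the formative survey, and Phase 1: Formative research uses the same figure of about 1,450 women for a survey that asks about PHC use. For that purpose PHC use is a sensible planning quantity. This stands in part: the label is real and has to be reconciled. But the calculation has experimental and control arms, 80% power and a control LGA, and it is the only sample size in the article. If it serves only the formative survey, the article shows no sizing for SBA at all.

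**A proportion of 50% is the cautious choice.** For a fixed absolute difference this is right. A reader might infer from setting 1,433 or 1,326 beside 659 that the wrong endpoint has halved the sample. The documents do not support that, because the two sides use different z terms.

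**One primary outcome is named.** This also stands. A reader might infer three rival primary outcomes and a headline left open until the data are seen. The article declares only SBA as primary. The PHC-use proportion is a planning parameter, and the phrase about skilled care through PHCs describes the aim of a regression.

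**The 50% may be defensible as stated.** The Abstract says the LGAs were chosen on "i) maternal mortality rates (ii) PHC utilization rates and (iii) and geographic localization", and Key research questions calls utilisation low. Both sit awkwardly with 50%. But selection could rest on routine records rather than published literature, and no local figure is given, so this is not a direct contradiction.

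**Conclusion.** The mismatch holds: the stated size and power belong to PHC use, and the declared primary outcome has neither. Its consequence is that power for SBA is unstated, not that the sample is too small because of the endpoint. Taken alone, the change of endpoint would reduce the requirement by about 8% to 15% for SBA rates around 33%.

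The low power at 659 per arm, about 44% for the plan's own scenario and about 48–51% for SBA at 38% v 33% or 33% v 28%, comes from the separate halving of 1.96. It also ignores clustering, for which the formula makes no allowance although the trial is cluster randomised. That too is a separate matter.

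The SBA figures rest on two assumptions: a 5-point difference that the article does not state for SBA, and a control rate near 33%, which is a national upper bound rather than a value for the Edo study area. The 25% v 20% row (1,090 per arm, power about 59%) shows how far a lower rate would shift them. The finding itself needs neither assumption; it rests on reading the two sections together.

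**What to change.** 1. Define one primary outcome and use it in both Data source and sampling and Statistical analysis plan. Either choice reconciles the text. If SBA is intended, rework the calculation for SBA and make PHC use secondary. If PHC use is intended, which would also fit the project's aim of increasing use of PHC services, correct the Statistical analysis plan.
2. If SBA is kept, take the control rate from the baseline survey. Failing that, use the national figure of under 33%, marked as an assumption and shown over a range. Then restate the detectable difference or the power for SBA at the planned size, with 1.96 unhalved and an allowance for clustering.
3. State whether the 1,450 sizes the formative survey, the trial comparison, or both.
4. Confirm that the questionnaire records who attended the birth. The article says only that women are asked whether they gave birth in the period and whether they used the PHC.
5. State how the regression on skilled care through PHCs relates to the primary outcome.

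The cost is wording and one recalculation. If the attendant is not recorded, an item must be added to the survey, and any round already completed without it could not supply an SBA rate.

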### Study design and setting

A community-based, multi-site, and multi-disciplinary cluster randomized trial using a mixed methods approach will be used. The project will be done in three phases: A formative phase (Phase 1) and an intervention phase (Phase 2), followed by evaluation of the intervention and policy transformation of the findings (Phase 3). The study will be conducted over 54-months in selected intervention communities, with selected communities of similar status serving as control sites. Surveys about maternal health services utilization will be carried out at baseline, at midterm and at end of the project to test the effectiveness of the intervention, alongside conventional epidemiological measures of maternal and perinatal mortality, each also collected in the three terms (Table 1).

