### Research objectives

This project aims to reduce maternal and perinatal mortality in Nigeria by strengthening the availability and use of maternal primary health care services by vulnerable women.

The specific objectives of the project are as follows:To identify the demand and supply factors responsible for use and non-use of primary health care for maternal health in selected communities in Edo State, Nigeria;Based on Objective 1, to derive and implement a set of multi-faceted community-led interventions to increase women’s access to antenatal, intrapartum and postnatal care services in primary health centres in six (6) randomly selected communities in six geo-political zones of the country;To evaluate the effectiveness of the implemented multi-faceted interventions by comparing both indicators of access to services, as well as maternal and foetal/new-born health outcomes, between the intervention-receiving communities vs. the control communities not receiving the intervention;To use the study findings to modify Nigerian policy and programmes aimed at increasing women’s access to evidence-based maternal and neonatal services, especially within the country’s rural areas.

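### The one analysis stated for the primary outcome is aimed at determinants of care, not at the intervention-versus-control comparison that the trial exists to make

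*Protocol article*

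**What the plan says.** All the analysis text is in the Statistical analysis plan section of the protocol article.

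- On the outcome it says "The primary outcome SBA will be analyzed", and then that the outcome data will be "aggregated to the cluster level and analyzed with regression model to examine the determinants of skilled pregnancy care using PHCs". No arm term, between-arm contrast or effect measure is named.
- On baseline it says "Baseline data will be summarized using descriptive statistics and percentages. No hypothesis testing will be performed on baseline data", and adds that "comparability of the LGAs will be evaluated from the perspective of clinically meaningful differences".

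Two other sections state what the trial is for.

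- Research objectives, objective 3: "To evaluate the effectiveness of the implemented multi-faceted interventions by comparing both indicators of access to services", together with health outcomes, "between the intervention-receiving communities vs. the control communities not receiving the intervention".
- Study design and setting: the design is cluster randomized, and the surveys are done "at baseline, at midterm and at end of the project to test the effectiveness of the intervention".

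**The concern.** The purpose of the regression is written into the sentence that specifies it, and that purpose belongs to objective 1 (why women do or do not use primary health centres). It is not objective 3 (whether the intervention works). An analyst who follows the section literally would report determinants of care and would have no pre-stated estimate for the randomized comparison. An arm contrast chosen after the data are seen would lack the protection of pre-specification.

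The method also fits its stated purpose poorly. Many of the determinants in the Theoretical framework section are characteristics of individual women. Once the data are averaged within communities, the coefficients describe how community averages vary together. They do not show how a woman's own age or education relates to her care.

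**Working it through.** No figure in the article is attached to the analysis sentence, so there is none to reproduce. The check compares target, level and available information.

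**Inputs**

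| Item | Value | Where |
|---|---|---|
| Trial communities | 6 intervention + 6 control = 12 | Abstract, Methods |
| Formative survey communities | 10 in each of 2 LGAs = 20 | Phase 1, Quantitative method |
| Respondents by LGA | 725 in an experimental LGA, 725 in a control LGA | Data source and sampling |
| Woman-level determinants | age, education, household size, previous pregnancies, health attributes | Theoretical framework |

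**1. Target.** Objective 3 needs the difference in SBA between arms. The stated regression is to examine determinants. These are different quantities, and only the second is named for the primary outcome.

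**2. Level.** For an arm comparison, the exposure (arm) is constant within a community if communities are allocated, so analysing community proportions loses nothing essential and respects the clustering. For woman-level determinants, the exposure varies within a community and aggregation discards that variation.

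**3. Residual degrees of freedom.** With K clusters and q covariates besides arm, df = K − 1 (intercept) − 1 (arm) − q.

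| K | Arm only (q = 0) | Arm + baseline SBA (q = 1) | Arm + 5 determinants | Arm + 8 | Arm + 10 |
|---|---|---|---|---|---|
| 12 | 10 | 9 | 5 | 2 | 0 |
| 20 | 18 | 17 | 13 | 10 | 8 |
| 2 (LGA as cluster) | 0 | not estimable | not estimable | not estimable | not estimable |

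An arm contrast is therefore feasible at community level, while a model with many determinants soon runs out of information at K = 12. The article does not say how many determinants would enter, so the last three columns are illustrations.

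**4. Baseline adjustment.** If baseline and endline community proportions correlate at r, adjustment multiplies the between-community variance by about 1 − r². The article gives no r. Over an assumed range: r = 0.3 gives 1 − 0.09 = 0.91; r = 0.5 gives 1 − 0.25 = 0.75; r = 0.7 gives 1 − 0.49 = 0.51. The price is 1 df (10 to 9).

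**5. Unit of allocation.** The Abstract and the objectives speak of communities. Data source and sampling puts one LGA in each arm.

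- If both arms occur in each LGA, a model with arm, baseline SBA and LGA has 12 − 1 − 3 = 8 df, and a permutation test within LGA exists.
- If each arm is one LGA, the arm and LGA indicators are identical. An LGA term cannot be fitted, no within-LGA permutation exists, and any arm difference is also the LGA difference.

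**The case against.** The strongest reply is that this is a condensed article, that the full analysis plan may state the arm contrast, and that nothing in the text excludes an arm term. The last part stands: a reader might infer that the plan cannot estimate the intervention effect, and the wording does not go that far. The rest does not remove the point. The article did not leave the primary analysis to another document. It stated one and gave it a purpose that conflicts with its own objective 3.

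Other stronger readings are tempting but not supported.

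- **That the plan ignores the baseline survey.** Baseline data are summarized and used to judge comparability. They are only not said to enter the outcome model, and covariate adjustment is commonly left to a fuller plan.
- **That aggregation is the error.** It is a recognized analysis for a trial with few clusters. The fault is the stated target.
- **That every determinant becomes ecological.** Supply-side factors such as staffing, equipment and drugs are assessed by facility checklist, so a community-level or facility-level analysis can suit them.
- **That the planned model has only 3 or 4 residual df.** This comes from counting seven determinants out of the theoretical framework (12 − 1 − 7 = 4, or 3 with arm). The article does not say that those seven enter.

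It is also fair to say that baseline SBA may not be available in every trial community. The formative survey covers 20 communities and asks about use of the primary health centre. The article does not say that the 12 trial communities are among the 20, or that SBA is recorded there.

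**Conclusion.** The point holds as a wrong stated target. The only analysis given for the primary outcome addresses determinants, while objective 3 and the purpose of the surveys require an intervention-versus-control comparison. For woman-level determinants, the stated aggregation yields only ecological associations.

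The consequence is the absence of any pre-stated effect estimate for SBA, not a numerical error. The information for a proper contrast is there on the Abstract's count of 12 communities: 10 residual df, or 9 with baseline SBA. Both figures assume that communities are the allocated units. With one LGA per arm there are two units and 0 df. The 25% to 49% variance reduction for r between 0.5 and 0.7 is an assumption about this population and not a property of the plan.

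**What to change.** 1. **Reconcile the unit of allocation first.** State whether communities or LGAs were allocated, and make the Abstract, objectives, sampling and analysis sections agree. Include an LGA term or a within-LGA permutation only if both arms occur in each LGA. If each arm is one LGA, say plainly that the arm effect cannot be separated from the LGA difference.
2. **Primary analysis.** Compare community-level endline SBA proportions between arms and report the risk difference with 95% CI. Base inference on the number of communities, by t (10 df with 12 communities) or by a permutation test that mirrors the actual allocation. Adjust for the community's baseline SBA proportion where the baseline survey measures it (9 df).
3. **Determinants.** Analyse woman-level determinants separately in an individual-level logistic model with a community random intercept, labelled exploratory. Facility-level supply factors can stay at their own level.

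**Cost.** Items 2 and 3 change analysis wording only and use the surveys already planned, at a price of 1 df for baseline adjustment. They depend on the surveys recording SBA in each trial community at baseline and endline, which should be confirmed.

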### Ethical clearance and registration

The ethical clearance approval needed for the project was obtained from the National Health Research Ethics Committee (NHREC) after the submission of the study protocol. The project ethical clearance certificate was approved on April 18, 2017, with NHREC Approval Number: NHREC/01/01/2007–18/04/2017. The protocol was also registered with ClinicalTrials.gov (Registration number is NCT02643953).

